### I. Recruitment

We will recruit study participants among 3rd trimester pregnant women receiving pre-natal care and women with newborns receiving post-natal care in San Pablo City. Educational and informational sessions will also be organized for midwives and other healthcare delivery personnel in San Pablo City. Through midwives, local healthcare providers, and the network of public health clinics, study advertisement and informational materials will be distributed to these women (Appendices C and D). Investigators will also hold community meetings several times per year for expectant mothers and parents of infants less than 14 weeks to discuss the study goals and potential risks and benefits. Details of study participation will be presented individually to each interested mother. The study protocol and consent forms in Tagalog will be reviewed in detail, questions will be addressed, and written informed consent will be obtained at study visit #1. Up until infant age of 14 weeks, there will be no pre-specified time limit for mothers to decide whether they would like to participate. The consent form in Tagalog will be signed by the mother, and witnessed by study personnel and another person. Participants may leave the study at any time without penalty.

### II. Scheduled visits

- i) Study Visit #1/Study entry- Mothers and infants will enter the study when the infant is between the ages of 6-14 weeks\*. We anticipate that the majority of infants will enter the study at ages 6, 10, or 14 weeks, when they are scheduled for one of their Extended Programme in Immunization (EPI) vaccinations (diphtheria/pertussis/tetanus, polio). After informed consent is obtained, data on the mother and the birth will be collected. In all infants, an anticoagulated blood sample will be collected upon study entry for plasma and peripheral blood mononuclear cells (PBMC) isolation. A serum sample from the mother will be collected at the same time or within 2 weeks of the infant blood sample.  
(\* Except on study initiation, when over the first 5 months of the study, infants between the ages of 6-24 weeks will be allowed to enter the study. This is to achieve an adequate sized study cohort for surveillance during the first dengue season).

**Data on mothers to be collected**

|                            |                                                                                                            |
|----------------------------|------------------------------------------------------------------------------------------------------------|
| Form data                  | Date, Study ID no, subject initials, Study Visit #, Location code                                          |
| Demographics               | Name, address, telephone, age, date of birth                                                               |
| Past medical hx            | Pre-eclampsia/eclampsia, gestational diabetes, tuberculosis (active), dengue (age of occurrence)           |
| Current medical conditions | Diabetes, asthma, lupus/autoimmune ds, tuberculosis (active), medications                                  |
| Birth/delivery             | gravida/para, normal vaginal delivery, complicated vaginal delivery, or C-section, transfusion at delivery |
| Feeding                    | Breastfeeding alone, breastfeeding+formula, formula alone; if breastfeeding, quantify times/24 h period    |

**Data on infants to be collected**

|                |                                                                                                                                              |
|----------------|----------------------------------------------------------------------------------------------------------------------------------------------|
| Form data      | Date, Study ID no, subject initials, Study Visit #                                                                                           |
| Demographics   | Name, age, date of birth, gender                                                                                                             |
| Past med hx    | Hospitalization between birth and current visit, reason, and location?
Febrile illnesses lasting >3 days between birth and current visit? |
| Medications    | Current medications                                                                                                                          |
| Measurements   | Height, weight, temperature                                                                                                                  |
| Vaccination hx | Vaccinations received to date from EPI card                                                                                                  |

- ii) Study Visit #2- Study Visit #2 will take place when the infant is between the ages of 4-6 months. At this time, data on infant health will be obtained. In all infants, an anticoagulated blood sample will be collected for plasma and PBMC isolation.

**Data on infants to be collected**

|                |                                                                                                                            |
|----------------|----------------------------------------------------------------------------------------------------------------------------|
| Form data      | Date, Study ID no, subject initials, Study Visit #                                                                         |
| Demographics   | Date of birth, gender                                                                                                      |
| Past med hx    | Hospitalization since last study visit, reason, and location?
Febrile illnesses lasting >3 days since last study visit? |
| Medications    | Current medications                                                                                                        |
| Measurements   | Height, weight, temperature                                                                                                |
| Vaccination hx | Vaccinations since last study visit from EPI card                                                                          |
| Feeding        | Breastfeeding alone, breastfeeding+formula/solids, formula/solids alone; if breastfeeding, quantify times/24 h period.     |

- iii) Study Visit #3- At age 15-16 months, 250 infants/year will be selected to return for a 3rd study visit. The 250 infants will be randomly selected from those without prior symptomatic dengue and whose study visits 2 and 3 span a significant portion of the peak DV transmission season (June-October). Data on infant health will be obtained and an anticoagulated blood sample for plasma will be collected.

**Data on infants to be collected**

|                |                                                                                                                            |
|----------------|----------------------------------------------------------------------------------------------------------------------------|
| Form data      | Date, Study ID no, subject initials, Study Visit #                                                                         |
| Demographics   | Date of birth, gender                                                                                                      |
| Past med hx    | Hospitalization since last study visit, reason, and location?
Febrile illnesses lasting >3 days since last study visit? |
| Medications    | Current medications                                                                                                        |
| Measurements   | Height, weight, temperature                                                                                                |
| Vaccination hx | Vaccinations since last study visit from EPI card                                                                          |
| Feeding        | Breastfeeding alone, breastfeeding+formula/solids, formula/solids alone; if breastfeeding, quantify times/24 h period.     |

III. Surveillance

- i) Hospitalized dengue- Surveillance for DV infections that result in hospitalization will occur year round and throughout the entire period of an infant's study participation (ages 6 weeks-16 months). Upon study enrollment, parents will be given a study identification card that will have their infant's unique identification number. When any infant in the study presents to one of the 7 hospitals serving San Pablo City, they will be identified as a study participant and their identification number and date/time of presentation will be transmitted to the study coordinating center at the City Health Office. Study personnel will then screen infants in the study who were admitted for acute febrile illnesses. Those infants will have history and clinical data abstracted, and an acute illness blood sample (serum) taken for dengue diagnostic testing. A convalescent blood sample (serum) will also be taken 10-14 days later.

**Data to be collected on infants hospitalized with acute febrile illnesses**

|                 |                                                                                                      |
|-----------------|------------------------------------------------------------------------------------------------------|
| Form data       | Date, Study ID no, subject initials, location code                                                   |
| Demographics    | Date of birth, gender                                                                                |
| Illness type    | Fever onset, symptoms, signs                                                                         |
| Hospital course | Clinical, laboratory, and radiographic data abstracted from medical record at end of hospitalization |

- ii) Non-hospitalized dengue- Each year during the peak DV transmission season from June to October, we will also conduct surveillance for DV infections that do not result in hospitalizations. During this time period, parents will be encouraged to bring their infants to the barangay health stations, local doctor's offices, or the City Health office if they develop an acute febrile illness. We will rely primarily on parents bringing their infants to the City Health office for febrile illnesses during the peak dengue season. In addition, nearly all pediatric health care providers in San Pablo will be aware of the study through education and information distributed through the local medical society and hospitals. Parents will be

reminded to present their study identification cards if they bring their infant with a fever > 38.0°C to a barangay health station or a private doctor's office. The health care personnel will be instructed to call a central telephone number where study personnel will coordinate transportation to the City Health office. There, study personnel will assess the infants, complete a questionnaire, and obtain an acute illness blood specimen (serum) for dengue diagnostic testing in addition to any routine clinical tests that may be requested by the treating nurse or physician. If the acute illness serum sample returns positive by DV IgM or RT-PCR, study personnel will arrange for collection of a convalescent blood specimen (serum) 10-14 days later.

#### IV. Outcomes

i) **Primary outcome- Identification of DV infection and classification of disease severity.**

Study subjects will be classified into the clinical categories shown in the table on the next page. Clinical categories I and II will be identified by surveillance for hospitalized dengue. Category III will be identified by surveillance for non-hospitalized dengue during the peak DV transmission season. Category IV will be identified by hemagglutination inhibition (HAI) seroconversion between study visits #2 and #3 in the 250 infants selected for blood sample collection at study visit #3.

ii) **Secondary outcome- estimation of peak viremia levels.**

We have previously found that viremia levels obtained within 72 hours of symptom onset in dengue are a good approximation of peak viremia levels [20-22]. A serotype specific, fluorogenic, quantitative RT-PCR assay will be performed on the acute illness serum samples collected within 72 hours of symptom onset from infants in Categories I-III.

| Clinical Category                                    | Diagnostic Criteria                                                                                                                              | Lab Diagnosis of DV infection                                                                              | Serotype of infection                  | Primary DV infection                                         |
|------------------------------------------------------|--------------------------------------------------------------------------------------------------------------------------------------------------|------------------------------------------------------------------------------------------------------------|----------------------------------------|--------------------------------------------------------------|
| I. Hospitalized DHF                                  | 1. Acute febrile illness* requiring hospitalization, and
2. Lab diagnosis of DV infection, and
3. Meets WHO criteria for DHF.              | 1. + DV RT-PCR from acute illness serum sample, or
2. + DV IgM from acute illness serum sample.         | Determined from RT-PCR                 | IgM/IgG EIA pattern in paired acute and convalescent samples |
| II. Hospitalized DF                                  | 1. Acute febrile illness* requiring hospitalization, and
2. Lab diagnosis of DV infection, and
3. Does not meet WHO criteria for DHF.      | 1. + DV RT-PCR from acute illness serum sample, or
2. + DV IgM from acute illness serum sample.         | Determined from RT-PCR                 | IgM/IgG EIA pattern in paired acute and convalescent samples |
| III. Non-hospitalized DF                             | 1. Acute febrile illness* brought to medical attention, and
2. No hospitalization, and
3. Lab diagnosis of DV infection.                   | 1. + DV RT-PCR from acute illness serum sample, or
2. + DV IgM from acute illness serum sample.         | Determined from RT-PCR                 | IgM/IgG EIA pattern in paired acute and convalescent samples |
| IV. Mild/asymptomatic DV infection (subset analysis) | 1. No symptomatic febrile illness during surveillance period identified as a DV infection, and
2. DV seroconversion over surveillance period. | 1. > 4-fold rise in anti-DV HAI Ab titers over scheduled blood draws encompassing the surveillance period. | Infer from neut Ab patterns to DVs 1-4 | Infer by age                                                 |
| V. No evidence of DV infection                       | none of the above                                                                                                                                |                                                                                                            |                                        |                                                              |

\* Temperature  $\geq 38.0^{\circ}\text{C}$ .

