### 7.4 Analysis Plan

I. ***First study objective- correlate pre-existing, maternally-derived, neutralizing Ab titers against the infecting DV serotype with disease severity.***

Subjects with hospitalized DHF will be rated as severity=5, and each step downward in severity category will be rated by a decrease in one point on a severity scale (4, 3, etc.). Neutralizing Ab titers determined in the pre-infection blood draws, and predicted neutralizing Ab titers at the time of illness based on a kinetic model of anti-DV Ab clearance (see below), will be used for analysis. The association between pre-existing neutralizing Ab titers (raw and log-transformed) and severity of DV infections will be evaluated by fitting partial proportional odds multivariate longitudinal models [28, 29]. When needed, we will also use generalized estimating equations [30, 31], clustering on patient observations over time, while using a logit link function and unstructured error correlation structure. Analyses will be performed separately

for each DV serotype, as well as with all serotypes pooled (and serotype included as a candidate term in the model).

We will also compare pre-existing, maternally-derived, neutralizing Ab titers against the infecting DV serotype to peak viremia levels measured in subjects with symptomatic dengue. In this subset, we will fit a multiple linear regression model for peak viremia with neutralizing Ab titer levels, and other potential covariates. Model selection will be by partial F-tests [32] on the difference in residual error.

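### Silent infections can be found only after visit 2 but symptomatic ones count from entry, which pulls the titre-severity association among infections toward the null

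*Protocol*

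**What the plan says.** **Symptomatic infection.** Section 4, II states: "Mothers and infants will enter the study when the infant is between the ages of 6-14 weeks" (up to 24 weeks during the first five months of the study). Surveillance for hospitalized dengue, Categories I and II, runs year round and "throughout the entire period of an infant's study participation (ages 6 weeks-16 months"). For milder illness, "Category III will be identified by surveillance for non-hospitalized dengue during the peak DV transmission season", at any study age.

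**Silent infection.** "Category IV will be identified by hemagglutination inhibition (HAI) seroconversion between study visits #2 and #3 in the 250 infants selected". On timing, "Study Visit #2 will take place when the infant is between the ages of 4-6 months" and "At age 15-16 months, 250 infants/year will be selected to return for a 3rd study visit". Those selected must be infants "whose study visits 2 and 3 span a significant portion of the peak DV transmission season (June-October"). The category table in Section 4, IV and the serology text in 6.2.1 describe the draws more loosely. The aliquot table in 6.2.1, however, provides HAI plasma at visits 2 and 3 and none at visit 1.

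**Analysis.** Section 6.2.1 measures neutralizing titres in the pre-infection draw of Categories I-IV. Section 7.4 I then says: "The association between pre-existing neutralizing Ab titers (raw and log-transformed) and severity of DV infections will be evaluated". It also plans titres predicted at the time of illness for symptomatic cases, and the titres at which 25%, 50% and 75% become symptomatic. It does not mention that the categories are found over different age ranges.

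**The concern.** Category IV is the infected-but-protected group, so it supplies the contrast that defines a protective titre. An infant silently infected between visits 1 and 2 already carries infection-induced antibody at visit 2. That infant is unlikely to show the required rise by visit 3, and so falls into Category V. An infant who becomes ill in the same weeks is counted as a case.

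The pre-infection draw sharpens the imbalance. A case before visit 2 brings a visit 1 titre, taken at 6-14 weeks. Every Category IV infant brings a visit 2 titre, taken at 4-6 months after further maternal antibody decay. The highest titres in the comparison therefore belong disproportionately to cases, with no silent infections beside them. This works against finding the association that the primary objective seeks. A perfect assay or full sampling after visit 2 would not bring the missing infections back.

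**Working it through.** **1. The plan's own counts (7.2).** Cohort 4,000 over 4 years = 16,000 infant-years. Hospitalized: 16,000 × 0.1-0.2% = 16-32; the stated 11 + 11 = 22 lies inside (22/16,000 = 0.1375%). Silent: 250 × 4 × 1-3% = 10-30; the stated 32 implies 3.2%, just above the range. Non-hospitalized: 44, with no stated rate to check. Total symptomatic 66; all infections 66 + 32 = 98.

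**2. Length of the unmatched window.** One month = 4.348 weeks, so visit 2 is at 17.4-26.1 weeks and 16 months is 69.6 weeks. Share = (visit 2 − entry)/(69.6 − entry).

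| Entry (weeks) | Visit 2 (weeks) | Window (weeks) | Share | Of 66 symptomatic, flat rate |
|---|---|---|---|---|
| 14 | 17.4 | 3.4 | 6% | 4 |
| 10 | 21.7 | 11.7 | 20% | 13 |
| 6 | 26.1 | 20.1 | 32% | 21 |

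Of the 32 expected silent infections, none can fall in this window. The flat-rate counts are probably high, because Section 2.1 reports few DHF cases under 3 months.

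**3. Titre gap.** The midpoint window is 11.7 × 7 = 82 days. With an assumed half-life of 60 or 30 days, titres fall 2^(82/60) = 2.6-fold or 2^(82/30) = 6.7-fold between visits 1 and 2.

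**4. Effect on the odds ratio (OR), run A.** Assumptions, none given in the Protocol: infection uniform over follow-up; log2 birth titre mean 9, SD 1.5; half-life 30-60 days; 67% of infections symptomatic (66/98); all silent infections after visit 2 found. The true OR is per doubling of titre at infection. The titre used is the last draw before infection.

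| True OR | Protocol window | After visit 2 only, visit 2 titre |
|---|---|---|
| 0.74 | 0.83-0.89 | 0.75-0.78 |
| 0.67 | 0.75-0.82 | 0.69-0.74 |

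Loss of log OR = 1 − ln(estimate)/ln(true). Under the Protocol it is 38-61% for 0.74 and 28-50% for 0.67. After restriction it is 4-17% and 7-25%.

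**5. Run B, with sampling as planned.** Silent infections are sampled 1 in 16 (4,000/250). Log10 birth titre mean 2.5, SD 0.6, floor 1:5. True OR 0.5 or 0.2 per log10 titre.

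| Half-life (days), true OR | Silent infections sought from entry | Protocol window | After visit 2 only |
|---|---|---|---|
| 30, 0.5 | 0.68 | 1.24 | 0.83 |
| 30, 0.2 | 0.54 | 0.99 | 0.79 |
| 45, 0.5 | 0.67 | 0.95 | 0.79 |
| 45, 0.2 | 0.49 | 0.68 | 0.64 |
| 60, 0.5 | 0.62 | 0.80 | 0.69 |
| 60, 0.2 | 0.36 | 0.46 | 0.44 |

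The Protocol window moves the OR upward in all six settings, and restriction moves it part of the way back. Before visit 2 the symptomatic share of recorded infections is 100%. It would be 44-59% if silent infections were sampled from entry.

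**6. The other titre definition.** Category IV has no infection date, so it can contribute only a visit 2 titre. In run A, setting predicted time-of-illness titres for cases against visit 2 titres for Category IV gives 0.44-0.53 for true values of 0.74 and 0.67. Restriction alone moves this to 0.30-0.36. In run B the same mixture gives 0.03-0.15. Here protection is exaggerated.

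**The case against.** **The comparator is open.** The severity scale drops one point per category, which puts Category V at 1, and Section 7.2 foresees 200 or 300 matched controls. If these form the reference, uninfected high-titre infants are present before visit 2 and the bias is small. This stands as a limit. Against it, 6.2.1 measures titres in Categories I-IV, and 7.4 I speaks of severity of infections. The 25/50/75% titres can also be read as a distribution over cases, which missing silent infections would not touch. The table in 7.1 lists titres at both visits; I have assumed that the last draw before infection is used.

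**Protection understated throughout.** A reader might infer this. Step 6 shows otherwise: the time-of-illness analysis, with visit 2 titres for Category IV, errs in the opposite direction.

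**Visit 3 selection as a cause.** A reader might infer that the season rule screens out infants exposed before visit 2. It hardly does. The interval between visits 2 and 3 is 15.5 − 5 = 10.5 months at midpoint ages, leaving 1.5 months of a year uncovered, so at least 5 − 1.5 = 3.5 of the five season months are spanned. At the extreme (6 to 15 months) the interval is 9 months and at least 5 − 3 = 2 are spanned.

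**Few early cases, and a matter for the SAP.** Early cases are few, but they carry the highest titres and so have leverage. An analysis-set restriction could sit in the SAP. The unequal windows, however, are fixed by the Protocol's visit schedule, aliquots and category definition. Section 6.2.2.1 also destroys samples from infants without infection who are not potential controls each year, so the missed infections may not be recoverable later.

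**Conclusion.** The concern holds for the comparison among infections (Categories I-IV) that uses pre-infection-draw titres. Infections recorded before visit 2 are symptomatic by construction, and this draws the titre-severity association toward the null. The direction was the same in every setting tried. The size was a 28-61% loss of the log odds ratio in run A, and in run B one setting passed 1. These sizes rest on assumed half-life, birth titre, effect size and uniform infection over follow-up.

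A reader might also infer that restricting to infections after visit 2 recovers the true odds ratio. With the titres this study can obtain, it does not; it removes much of the distortion in run A and less in some settings of run B. It aligns age at infection only. Category IV still comes from a sample of 250 a year while Categories I and II come from the whole cohort, which is a separate matter. The point should be fixed, but it does not invalidate the design.

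**What to change.** In 7.4 I, state the following:

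- Compare Categories I-III with Category IV using only illnesses with onset after the infant's visit 2. Apply the same restriction to any 25/50/75% titre that uses Category IV in its denominator.
- In that comparison, use the visit 2 titre for both cases and Category IV. Do not set predicted time-of-illness titres for cases against visit 2 titres for Category IV.
- Report illnesses before visit 2 descriptively, with their visit 1 titres.
- State that the resulting protective titres are visit 2 titres and apply to infection after visit 2.

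This needs no new samples or visits. The cost is the symptomatic cases before visit 2, roughly 5-15% on the assumed inputs (66 × 0.05 to 66 × 0.15, about 3 to 10 cases), and a conclusion that does not cover the first 4-6 months of life.

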#### Surveillance (hospitalized or non-hospitalized dengue surveillance)\*

| Time point                             | Blood collection volume     | Aliquots/Assays                                                                                        |
|----------------------------------------|-----------------------------|--------------------------------------------------------------------------------------------------------|
| Acute illness sample                   | 3 ml (serum separator tube) | Serum: 0.25 ml IgM EIA, 0.25 ml RT-PCR, 1.0 ml for repeat assays/future RT-PCR and IgM/IgG EIA/storage |
| Convalescent sample (10-14 days later) | 3 ml (serum separator tube) | Serum: 0.5 ml for IgM/IgG EIA, 1.0 ml for repeat assays/storage                                        |

\* Participating infants cannot have > 2 paired (acute and convalescent) surveillance blood samples taken while in the study.

The proposed amount of blood drawn from study participants poses no more than minimal risk as defined by Office of Human Research Protections guidelines [19]. The amount of blood drawn does not exceed the lesser of 50 ml or 3 ml/kg in an 8 week period and collection does not occur more frequently than 2 times/week.

Assay descriptions:

**Virus RT-PCR-** A qualitative, serotype specific, DV RT-PCR assay will be performed on all acute illness serum samples. The assay technique has been previously published [23]. Results will be available within 3 days, and outpatient subjects with a positive DV RT-PCR will have a convalescent blood sample collected. Paired acute and convalescent serology will be performed to confirm primary DV infections (see below).

**Serology-** An anti-DV IgM EIA will be done on all acute illness serum samples collected. The results will be available within 3 days, and outpatient subjects with a positive DV IgM will have a convalescent blood sample collected. Paired acute and convalescent sera will be tested for anti-DV IgM/IgG by EIA using standard techniques and criteria to confirm primary DV infections [24].

At the conclusion of the year, plasma samples from the 250 subjects with 3 scheduled study visits will be identified. These subjects will not have had an earlier recognized symptomatic DV infection. The plasma samples that span a significant part of the peak DV transmission season will be tested for anti-DV Abs by HAI serology [25] to identify those with clinically unrecognized seroconversions.

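### Laboratory diagnosis of hospitalised dengue ignores the convalescent serum, so an infant negative on the acute sample who seroconverts on the pair is classed as uninfected (occasionally as mild)

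*Protocol*

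**What the plan says.** Section 4, III (Surveillance) treats the two settings differently. For infants admitted with an acute febrile illness, an acute serum is drawn and then "A convalescent blood sample (serum) will also be taken 10-14 days later", with no condition on the acute result. For outpatients the second draw is conditional: "If the acute illness serum sample returns positive by DV IgM or RT-PCR, study personnel will arrange for collection of a convalescent blood specimen".

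Section 6.2.1 (Serology) states what is done with the pairs: "Paired acute and convalescent sera will be tested for anti-DV IgM/IgG by EIA using standard techniques and criteria to confirm primary DV infections". The surveillance sample table in the same section sets aside convalescent serum for that assay.

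The clinical category table in Section 4, IV gives Categories I to III the same two laboratory criteria. One is a positive "DV RT-PCR from acute illness serum sample", the other a positive "DV IgM from acute illness serum sample". The paired result, "IgM/IgG EIA pattern in paired acute and convalescent samples", stands only in the column on primary infection. Category IV requires that there was "No symptomatic febrile illness during surveillance period identified as a DV infection", together with a "4-fold rise in anti-DV HAI Ab titers over scheduled blood draws encompassing the surveillance period". Category V is the remainder.

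**The concern.** The protocol collects a second serum from every screened hospitalised infant (up to its limit of two pairs per infant) but gives that serum no part in deciding whether the infant had dengue. The table is also uneven. A rise between two scheduled samples is enough to diagnose the mildest class of infection, while a rise between two illness samples does not count for the most severe classes.

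This is the primary outcome (Sections 4, IV and 7.1), and hospitalised dengue is among its scarcest levels: Section 7.2 expects 11 DHF and 11 hospitalised DF cases in four years. An infant wrongly placed in Category V meets three further rules:

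- Section 6.2.1 assigns the pre-infection neutralisation, ADE and PBMC assays to Categories I-IV. Category V gets only small PBMC and T-cell optimisation subsets, plus the antibody-kinetics sample in Section 7.4.
- Section 6.2.2.1 allows yearly destruction of samples from uninfected infants who are not potential matched controls, so the loss may be irreversible.
- Section 7.2 draws matched controls from infants without evidence of infection, and the DHF regression in Section 7.4 uses subjects of lower severity as controls.

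**Working it through.** **Trace of one infant.** Take an infant admitted with fever whose acute RT-PCR and acute IgM are both negative and whose paired EIA shows seroconversion.

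1. Categories I and II both require laboratory diagnosis, and both criteria are tied to the acute sample. Neither category is met.
2. Category III requires that there was no hospitalisation. It is not met.
3. Category IV applies only if the infant is among the 250 per year seen at visit 3 and shows the HAI rise. Its first criterion excludes febrile illness only where that illness was identified as DV infection. On a literal reading this illness was not.
4. Otherwise the infant is Category V.

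On the Section 7.1 scale (I = 5, II = 4, III = 3, IV = 2, V = 1), the score falls from 5 or 4 to 1, or occasionally to 2. No other section lets the paired result change the category.

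**The protocol's planning figures.** A cohort of 4,000 over 4 years at 0.1-0.2% gives 4,000 x 4 x 0.001 = 16 to 4,000 x 4 x 0.002 = 32 hospitalised cases. The stated 11 + 11 = 22 corresponds to 22 / 16,000 = 0.1375%, inside that range. The four expected counts sum to 11 + 11 + 44 + 32 = 98, in line with the stated total of nearly 100.

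**Cases missed.** Section 7.2 describes the 22 as cases it anticipates capturing, so missed cases come on top of them. Let s be the combined sensitivity of acute RT-PCR or IgM. The protocol does not give s; 0.80-0.95 is an assumption, taken to be the same for DHF and DF. Then missed = 22/s - 22, and for DHF alone 11/s - 11.

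| Assumed s | Hospitalised cases missed | Of which DHF |
|---|---|---|
| 0.95 | 23.16 - 22 = 1.2 | 11.58 - 11 = 0.6 |
| 0.90 | 24.44 - 22 = 2.4 | 12.22 - 11 = 1.2 |
| 0.80 | 27.50 - 22 = 5.5 | 13.75 - 11 = 2.8 |

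**How many reach Category IV.** Visit 3 covers 250 x 4 = 1,000 of about 10,000 infants, or 10% on average. That gives at most about 1.2 x 0.10 = 0.12 to 5.5 x 0.10 = 0.55 infants, before requiring the HAI rise. The share could be higher among infants whose visits span the season.

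**How many become matched controls.** Drawing 200-300 controls at random from about 10,000 gives each infant a 2-3% chance: 1.2 x 0.02 = 0.02 to 5.5 x 0.03 = 0.17 contaminated controls. Matching could change this.

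**The case against.** The strongest defence is that one laboratory rule for Categories I to III is a deliberate and sound choice. Outpatients give a convalescent serum only if already positive, so admitting paired evidence for inpatients alone makes the detection of infection depend on hospitalisation, which is itself part of the severity scale. That is a real drawback. A sensitivity analysis on acute-positive cases shows whether it matters. It does not justify recording an infant with a documented seroconversion as uninfected.

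Second, the stated purpose of the paired EIA is to confirm primary infection, which can be read as typing cases already diagnosed. The protocol does not expressly say that pairs from acute-negative infants are run. This stands as an ambiguity. But the serology text is not limited to acute-positive infants, and on the narrow reading the hospital convalescent draw in an acute-negative infant has no stated use. Either reading calls for a correction.

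Third, added cases would be RT-PCR negative, with no serotype and no quantitative viremia. This is correct and limits the gain: they cannot enter the serotype-specific or viremia models as specified. The protocol already accepts cases positive only by IgM, which have the same limitation, and the DHF regression pools serotypes.

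Fourth, the Category IV route is narrow, and staff might treat such an illness as recognised dengue and not select the infant for visit 3. That is fair. Category V is the default outcome and IV the exception.

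**Conclusion.** The gap is real and lies in the case definition itself. Followed as written, the table puts a hospitalised infant with paired seroconversion and a negative acute sample into Category V, or possibly IV. The main effect is loss of scarce hospitalised and DHF cases, with a small risk of contaminated controls. At an assumed acute sensitivity of 80-95%, about 1.2-5.5 hospitalised cases would be missed beyond the 22 expected. The count rests wholly on that assumption; the classification problem does not.

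Two stronger readings are not supported:

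- A reader might infer that the titre-severity slope is biased toward zero. An infant in Category V normally has no titre measured under Section 6.2.1, and the first-objective model in Section 7.4 concerns the severity of DV infections. Such an infant mostly drops out, which costs precision. If missed cases differ in antibody titre from detected ones, bias could go either way.
- A reader might infer that some of the 22 expected cases are themselves misclassified. Section 7.2 counts those as captured, so the missed cases are additional.

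**What to change.** 1. In rows I and II of the category table, add a third laboratory criterion: IgM seroconversion, or a diagnostic IgM/IgG rise, between the acute and convalescent sera by the EIA already planned. State in Section 6.2.1 that this EIA is run on all hospitalised pairs, whatever the acute result.
2. Bar infants who meet this criterion from Categories IV and V, from the control pool, from visit 3 selection and from yearly sample destruction.
3. Record serotype as unknown when RT-PCR is negative. These cases then enter only the pooled analyses, including the DHF regression, and not the serotype-specific or viremia models.
4. Add a sensitivity analysis restricted to cases positive on the acute sample, because outpatients have no equivalent paired evidence.

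If paired evidence is left out on purpose, the protocol should give the reason and still keep these infants out of the control pool.

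The cost is small. The sera and the assay are already in the plan. The changes are to wording, plus making paired results available before visit 3 selection and before the yearly destruction of samples. The remaining downside is slightly more complete ascertainment in hospitalised than in outpatient cases.
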